### MRI brain morphology and microstructure

MRI data will be collected on a 3 Tesla MRI Siemens Connectom system with ultra-strong (300 mT/m) gradients. Ultra-strong gradients allow the acquisition of diffusion-weighted data with high diffusion-weighting b-values, with good signal-to-noise ratio for the estimation of intracellular diffusion properties.^32^ Multishell high angular resolution diffusion imaging (msHARDI)^33^ data (max b-value=6000 s/mm^2^) will be acquired to estimate microstructural white and grey matter properties of neurite and soma density and soma size.^34 35^ Myelin properties will be estimated with quantitative magnetisation transfer (qMT) imaging^36^ and multicomponent-driven equilibrium single pulse observation of T_1_ and T_2_ (mcDESPOT).^37^
Table 3 provides details of the MRI protocols including their acquisition parameters, the outcome index maps from the analysis based on biophysical modelling, and the estimated white and grey matter tissue properties.

**Table 3 T3:** Overview of MRI data

MRI sequences	Acquisition parameters	Rationale and outcome indices
Magnetisation-prepared rapid gradient-echo (MP-RAGE)	1 mm^3^ resolution, FOV: 256×256, TR=2300 ms, TE=2 ms, TI=857 ms, flip angle: 9; Duration~7 min	3-dimensional (3D) T_1_-weighted anatomical image For the segmentation of regions of interests in the basal ganglia, sensori-motor cortices and cerebellum As reference map for all microstructural outcome maps
Multi-shell High Angular Resolution Diffusion Imaging (msHARDI)^33^	2 mm^3^ resolution; FOV: 220×200; matrix size: 110×110 x 66; TE/TR=59/3000 ms; δ/Δ: 7/24 ms; b-values=0 (14 volumes), 500 (30 directions), 1200 (30 directions), 2400 (60 directions), 4000 (60 directions) and 6000 (60 directions) s/mm^2^; Duration ~20 min	Multishell diffusion weighted imaging data For multitissue constrained spherical deconvolution-based^54^ tractography to reconstruct white matter pathways of interest (corpus callosum, cortico-spinal tract, connections between caudate and prefrontal cortex, connections between putamen and supplementary motor area/motor cortex) For modelling of white matter tissue properties with the Composite Hindered And Restricted Model of Diffusion ^41^ yielding the restricted signal fraction (FR) as an estimate of axon density and the Neurite Orientation Dispersion and Density Imaging^42^ yielding the isotropic signal fraction as an estimate of free water and the orientation dispersion index as an estimate of axon orientation and dispersion. for modelling of grey matter tissue properties with the Soma And Neurite Density Imaging model^35^ yielding estimates of soma density (soma signal fraction) and size.
Quantitative magnetisation transfer (qMT)^55 56^	1.72 mm^3^ resolution; FOV 220×220×179 mm; matrix size 128×128 x 104; turbo flash sequence, turbo factor 4, non-selective excitation MT pulse duration: 15.3 ms, 11 MT-weighted volumes and 1 vol without MT-weighting, 11 Frequency offsets (Hz) and 11 flip angles (degrees): 47 180 (628°); 56 360 (332°); 12060, (628°); 1000 (332°);1000 (333°); 2750 (628°); 2770 (628°); 2790 (628°); 2890 (628°); 1000 (628°); 1000 (628°); Duration ~25 min	qMT data to model the macromolecular proton fraction as an estimate of white matter myelin content^36^.
Multicomponent-driven equilibrium single pulse observation of T_1_ and T_2_ (mcDESPOT)^37^	1.72 mm^3^ resolution; FOV 220×220×179 mm; matrix size 128×128×104;T1-weighted 3D spoiled gradient-recalled echo sequence (SPGR) with TR=4 ms; TE=1.9 ms; 8 flip angles (3°, 4°, 5°, 6°, 7°, 9°, 13° and 18°); Inversion recovery-prepped spoiled gradient-recalled echo sequence with TR=4 ms; TE=1.9 ms; flip angle 5°; steady-state free precession with TR=4.54 ms, TE=2.27 ms, 8 flip angles (10°, 13.33°, 16.67°, 20°, 23.33°, 30°, 43.33° and 60°), duration ~14 min	mcDespot data to model The myelin water fraction as an estimate of white matter myelin To estimate T_1_ and B_1_ fields for qMT analyses

FOV, field of view; mcDESPOT, Multicomponent Driven Equilibrium Single Pulse Observation of T1 and T2; MT, magnetisation transfer; TE, echo time; TI, inversion time; TR, repetition time

All MRI protocols have been piloted in individuals with HD. They take 60 min in total to acquire and are well tolerated. Our previous research has identified microstructural differences in HD patients compared with healthy controls.^38 39^ Importantly, we found drumming training-induced increases in the qMT-based macromolecular proton fraction in callosal WM suggestive of increased myelin.^19^

### Sample size

Following the Consolidated Standards of Reporting Trials (CONSORT) statement extension to randomised pilot and feasibility trials,^40^ no formal power calculations have been conducted. We aim to recruit 50 individuals with HD. This number is pragmatic given the size of the target population, level of engagement required and resources available. It will allow estimation of recruitment, retention and adherence rates with a 95% binomial CI of no more than plus or minus 15 percentage points irrespective of the point estimate.

The combined population of the participating patient identification centres (PICs) should be adequate to achieve recruitment target, but this assumption will be tested as part of the feasibility assessment. While there is facility to add more PICs, further strategies to enhance recruitment will not be used within this feasibility trial.

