### Trial design

We will conduct a two-arm randomised controlled feasibility trial of individuals with HD randomised to 8 weeks of HD-DRUM intervention or usual-activity control (figure 1).

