**Figure 2 F2:**
[figure not shown]
The HD-DRUM app environment. (A) The app home screen interface that allows users to navigate through and select unlocked training sessions. (B) The virtual drums, a blue triangle (high pitch bongo) and red circle (low-pitch bongo), participants use to tap in synchronisation with the audio instructions.

Participants in the intervention group will be provided with a tablet with the HD-DRUM app installed and an instruction manual for home use. Following completion of baseline assessments participants will receive a face-to-face introduction to the app to familiarise themselves with HD-DRUM. To support retention of the intervention, researchers will maintain weekly contact with participants to provide feedback, assist with any queries or problems and help remove potential barriers. Whenever possible, family members and/or carers will be encouraged to support engagement with the training. Participants will report what support they found helpful in an intervention evaluation questionnaire. Participants in the control condition will be offered the opportunity to borrow a tablet with HD-DRUM to try the training out after they have completed the final assessment of the study.

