### Statistical methods

The study will be reported in accordance with the CONSORT statement extension to randomised pilot and feasibility trials.^40^ As this is a feasibility trial, it is not formally powered to test for effectiveness of the intervention while controlling type I error. The primary aim is to assess the feasibility. For this purpose, recruitment, retention and adherence rates and acceptability rating scores and thematic responses will be documented and evaluated according to the success criteria described above. Feasibility percentage rates will be calculated as follows:

Recruitment rate=100×(number of participants consented/number of participants eligible and approached) %.Retention rate=100×(number of participants completing the study at 8-week follow-up/number of participants consented) %.Adherence rate (frequency)=100×(number of days app used for training/40 days) %.Adherence rate (duration)=100×(number of minutes app used for training /(40 days×11.3 min average session duration=451 min) %.

Descriptive summaries such as mean and SD estimates (for continuous variables) of effect sizes and 95% CIs will be calculated for all secondary clinical and MRI outcome measures. Motor and mood measurements are detailed in the outcome section above and information about the cognitive and MRI outcome measures can be found in tables2  3. Differences in mean and SD of participants’ absolute and percentage changes from baseline will be calculated to provide estimates of effect size and variability of any performance changes in the two groups. All calculations will be conducted in SPSS^43^ and R.^41^ This will provide information to help estimate the sample size required for a future definitive RCT into HD-DRUM in this patient population. Note that the absence of a change in individuals with HD in the HD-DRUM group compared with the control group may suggest a beneficial effect of the intervention as HD is a progressive neurodegenerative disease.

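### The ±15-point binomial precision stated for 50 participants holds for recruitment and retention but is not guaranteed for adherence, which is observed in the HD-DRUM arm only and is not a count of participants

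*Protocol article*

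**What the plan says.** All references are to the protocol article.

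- **Sample size.** No formal power calculation was done and the number is called pragmatic: "We aim to recruit 50 individuals with HD". The section then states what this number delivers: "estimation of recruitment, retention and adherence rates with a 95% binomial CI of no more than plus or minus 15 percentage points". The limit is said to apply at any value of the estimated rate.
- **Trial design.** There are two arms, "individuals with HD randomised to 8 weeks of HD-DRUM intervention or usual-activity control". The article does not state the allocation ratio.
- **Intervention** (text after the Figure 2 caption). "Participants in the intervention group will be provided with a tablet with the HD-DRUM app installed". Controls may "borrow a tablet with HD-DRUM to try the training out after they have completed the final assessment of the study".
- **Primary feasibility outcome assessments.** The app itself logs adherence. The traffic-light rule is green if all feasibility rates are at least 70% and red if any is below 40%.
- **Statistical methods.** Recruitment is consented over eligible and approached. Retention is completers over consented. Adherence by frequency is "Adherence rate (frequency)=100×(number of days app used for training/40 days", as a percentage. Adherence by duration is minutes of use over 451 minutes. The article has no rule that classes a participant as adherent or not.

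**The concern.** One precision statement covers three kinds of rate, but they share neither a denominator nor a distribution. The ±15 figure is a property of a binomial proportion observed on about 50 people. Retention has that denominator and recruitment has at least that many. Adherence has neither the 50 people nor the binomial form: controls have no app to log until their final assessment is over, and days out of 40 or minutes out of 451 are amounts of use.

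Feasibility is the primary objective, and the precision sentence is the only quantitative statement made in support of the sample size. Adherence supplies two of the four rates calculated in Statistical methods, and under the traffic-light rule a single rate can block green or trigger red. A reader judging how firmly an adherence result near 70% can be taken would rely on a precision that the design does not secure.

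**Working it through.** **Inputs.** N = 50 and the 95% binomial CI of at most ±15 points (Sample size); app access in the HD-DRUM arm only (Intervention); adherence as days/40 and minutes/451 (Statistical methods). Assumed, because the article does not give them: 1:1 allocation, so about 25 in the HD-DRUM arm, with 33 (about 2:1 in favour of HD-DRUM) as a check; and the between-person SD of adherence.

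**Step 1. Reproduce the plan's figure.** The worst-case Wald half-width for a proportion is 1.96 × √(0.25/n). At n = 50 it is 1.96 × √(0.25/50) = 13.9 points. The largest Clopper-Pearson (exact) half-width over all possible counts is 14.5 points, and the largest Wilson half-width is 13.4. All are within 15, so the stated figure is right for a denominator of 50.

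**Step 2. Recruitment and retention.** If 50 consent, retention has a denominator of 50, as in step 1. Recruitment has a denominator of at least 50. At a 70% rate, for example, about 50/0.70 = 71 are approached, and the half-width is 1.96 × √(0.7 × 0.3/71.4) = 10.6 points. The statement holds for both.

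**Step 3. Adherence, if it were a binomial proportion of participants.**

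| n with the app | Wald | Exact | Wilson |
|---|---|---|---|
| 50 (as the statement implies) | ±13.9 | ±14.5 | ±13.4 |
| 33 (about 2:1) | ±17.1 | ±17.8 | ±16.1 |
| 25 (1:1) | ±19.6 | ±20.4 | ±18.2 |

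The smallest n that keeps the worst case within 15 points is 43 (Wald), 47 (exact) or 39 (Wilson). Neither 25 nor 33 reaches any of these.

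Nor is the limit met irrespective of the point estimate. At n = 25, 1.96 × √(p(1−p)/25) ≤ 0.15 requires p(1−p) ≤ 0.146, that is p above about 82% or below about 18%. At the green threshold of 70% the half-width is 1.96 × √(0.21/25) = 18.0 points.

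**Step 4. Adherence as the mean of per-person percentages.** This is the reading closest to Statistical methods. With 25 people the 95% t-interval half-width is 2.064 × SD/√25 = 2.064 × SD/5.

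| Assumed SD (points) | Half-width |
|---|---|
| 20 | ±8.3 |
| 30 | ±12.4 |
| 40 | ±16.5 |

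Setting 2.064 × SD/5 = 15 gives SD = 75/2.064 = 36.3. The mean is therefore within ±15 points if the SD is about 36 or less. The article gives no SD, so whether the limit is met cannot be settled from it.

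**The case against.** The best counter-arguments are these.

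- **The sample size is pragmatic.** The precision sentence describes what 50 people give and does not derive the 50. Removing adherence from it would leave N unchanged. This stands and limits the consequence. It does not make the sentence correct: a pragmatic number needs no power calculation, but a precision that is stated should be true.
- **No decision uses the interval.** The traffic-light rule compares rates with 70% and 40% and mentions no CI. This also stands. The misstatement affects how firmly a colour can be read, not which colour is computed.
- **Mean adherence may be precise enough.** A reader might infer that the trial cannot estimate adherence to within ±15 points. The documents do not support that. As a mean over 25 people, adherence meets ±15 at any SD up to about 36. For a measure running from 0 to 100% with mean 70%, the largest possible SD is √(0.7 × 0.3) = 46 points, so missing the limit would need a nearly all-or-none pattern of use. The error is a guarantee that does not follow from N = 50, not a demonstrated lack of precision.
- **The ±20 figure rests on an outcome that the article does not define.** The 70% and 40% cut-offs apply to trial-level rates, and there is no threshold for classing one person as adherent. The figure therefore shows what the words binomial CI would imply on this arm. It is not the trial's adherence precision.

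A reader might also suppose that daily use would be pooled into one large binomial sample across participants. Nothing in the article proposes this, and the binomial CI appears only in the Sample size section. The criticism is confined to that sentence and does not extend to an analysis method that may be set out elsewhere.

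**Conclusion.** The sentence is wrong as written for adherence and right for recruitment and retention. For adherence it counts people who have no app during the study and applies a binomial interval to a quantity that is not a count of participants. Read literally, as a binomial proportion, the worst case is about ±20 points on 25 people, or about ±17 to ±18 (Wald and exact) on 33, against the stated ±15. Read as a mean of per-person percentages on 25 people, ±15 is met or missed according to whether the SD is below or above about 36 points.

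The figure of 25 assumes 1:1 allocation and no loss of adherence data. The failure of the binomial guarantee does not depend on exactly 1:1, since about 2:1 in favour of HD-DRUM also falls short. The SDs are assumptions. The point concerns a stated precision; it does not show that 50 participants are too few.

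**What to change.** In Sample size, limit the ±15-point binomial statement to recruitment and retention. State the allocation ratio and the expected number in the HD-DRUM arm.

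Give adherence precision in a separate sentence, for the HD-DRUM arm only, as a participant-level t or bootstrap CI for mean adherence, with the SD declared as an assumption. If allocation is 1:1, suitable wording would be: with about 25 participants using HD-DRUM, mean adherence would be estimated to within about ±12 points if the between-participant SD is 30 percentage points, and about ±17 points if it is 40.

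Quote about ±20 points only if a definition of an adherent participant is added, because the article has none.

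The cost is wording. The precision claimed for adherence becomes conditional and less favourable; the sample size, the data collected and the traffic-light thresholds are unchanged, and no extra patients are needed.

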### Assignment of interventions

#### Allocation

Randomisation will be stratified for TFC score to ensure comparability of the groups with regard to disease burden. There will be five strata corresponding to TFC scores of 9, 10, 11, 12 and 13, respectively. One randomised group allocation sequence per stratum will be computer generated based on pseudo-random numbers by a statistician [name] independent of patient recruitment and data collection, using R V.4.1.0^41^ and uploaded onto the HD-DRUM project-specific Research Electronic Data Capture (REDCap)^42^ site.

#### Blinding (masking)

The researchers conducting the baseline assessments (cognitive, motor and MRI) have no access to the randomisation list implemented in REDCap and will be blind to the group allocation until baseline assessments are completed. However, once group allocation has taken place at the end of the baseline assessments, blinding of the researchers involved in the data collection and participants will not be possible due to the nature of the intervention and control conditions and due to limited resources and staffing. The analysis of the Q-Motor data will be conducted blind to group allocation by an independent researcher not involved in the data collection [name]. The lack of blinding of the clinical and MRI outcomes is a limitation of the study design, but quantitative outcome measures have been used where possible to minimise any potential biases that may be introduced due to a lack of blinding.

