#### Data management

Participants will be assigned a study and CUBRIC ID and all electronic and hard copy data will be coded with these IDs. Electronic data will be stored within Cardiff University’s firewall and password-protected computer systems. Cognitive and motor clinical outcome and training data (stored in .csv files) will be managed with the REDCap web application (www.project-redcap.org) that allows secure storage, management and sharing of data using a confidential security level. Paper record forms will be scanned, and electronic copies will be uploaded onto RedCAP. Cognitive and motor scores are entered by the researcher [name] and will be quality-checked against the original record forms by other members of the research team.

The data collection with the drumming training application complies with General Data Protection Regulation (GDPR) and data privacy regulations. No personal or identifiable user information is stored on the tablet or on Google Firebase. The drumming training output files are coded with a sixteen-digit-letter-string tablet ID. Firebase services encrypt data at rest and during transit using hypertext transfer protocol secure.

MRI data will be stored securely on the CUBRIC partition of XNAT (www.central.xnat.org). Study and CUBRIC ID keys and any personal information will be stored for the duration of the project securely in a locked cupboard in the principal investigator’s [name] office in CUBRIC. Only researchers associated with the study will have confidential access to files, which allow the matching of recorded data to participants. No data, whether paper or electronic, will leave Cardiff University sites without being completely coded, that is, all identifiable data will be removed from the dataset. Any electronic files or disks will be stored on Cardiff University sites and electronically on Cardiff University systems. At the conclusion of the study, participant-identifiable data will be destroyed and non-identifiable data will be archived, although it will still be accessible to the study team. Data will be archived for 15 years, in line with Cardiff University policies and procedures.

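### MRI outcomes are accepted as unblinded for reasons that do not reach offline image processing, although the Q-Motor analysis in the same trial is masked

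*Protocol article*

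**What the plan says.** All statements are in the Protocol article.

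- **Blinding (masking).** Assessors are blind until baseline testing, including MRI, is finished. After allocation, "blinding of the researchers involved in the data collection and participants will not be possible due to the nature of the intervention and control conditions". The section adds a second reason, that this is "due to limited resources and staffing". One analysis is then protected: "The analysis of the Q-Motor data will be conducted blind to group allocation by an independent researcher not involved in the data collection". MRI is not protected: "The lack of blinding of the clinical and MRI outcomes is a limitation of the study design". The mitigation offered is that "quantitative outcome measures have been used where possible to minimise any potential biases".
- **MRI brain morphology and microstructure, Table 3.** T1-weighted images are used to segment regions of interest. The diffusion data are used for "tractography to reconstruct white matter pathways of interest". Indices then come from biophysical models.
- **Data management.** All data carry study and CUBRIC IDs, MRI data are held on XNAT, and the ID keys are locked away. Researchers on the study can have access to the files that match data to participants.
- **Allocation.** The sequences are generated by a statistician who takes no part in recruitment or data collection.

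**The concern.** Unblinded participants and unblinded face-to-face testers are hard to avoid with a training app compared with usual activities. Processing stored scans is a different stage: it needs no contact with the participant and no knowledge of arm. The article gives reasons for the first situation and then applies the resulting limitation to MRI outcomes as a whole.

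What is at stake is the between-arm comparison of microstructural change. The secondary objectives use it to explore mechanism, and the Abstract also lists brain microstructure among the changes evaluated to obtain effect sizes for planning. The team reports an expected direction from its pilot work, an increase in the callosal macromolecular proton fraction after drumming. An expected direction, small arms and processing that is not masked together are the conditions in which masking is worth having.

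**Working it through.** The plan gives no figure for this point, so the check is mainly a comparison of statements.

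1. **Whom the reasons cover.** The sentence on impossibility names participants and researchers involved in data collection. Both reasons, nature of the conditions and limited resources, attach to that sentence. People who process images after acquisition are not named, and no separate reason is offered for them.

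2. **Q-Motor as comparator.** Q-Motor participants and testers are as unblinded at follow-up as those in the MRI session. The two outcomes therefore differ in protection only at the analysis stage. The plan treats masking at that stage as possible for one outcome and does not extend it to the other.

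3. **Whether existing coding already masks.** It does not do so by itself. The coded ID is the study's own, and study researchers can have access to the matching files. Whether the people who process the images use that access, or know allocation by another route, is not stated.

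4. **Whether there is a route for bias.** Region segmentation and pathway reconstruction precede every regional or tract-based index, so a numerical end product does not remove judgement made upstream. Table 3 does not say whether these steps are manual, semi-automated or automated. The article describes no rule for rejecting scans. The route is therefore conditional: it exists if any of these steps involves operator judgement, and is small or absent if all are automatic.

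5. **What depends on it.** The traffic-light criteria under Primary feasibility outcome assessments use feasibility rates, and the rates defined under Statistical methods cover recruitment, retention and adherence. None uses MRI data. The MRI outcomes enter as descriptive means, SDs, effect sizes and 95% CIs.

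6. **Size.** It is not computable: the document gives no inter-operator error, exclusion rate or SD. A hypothetical case shows only the scale. Assume 20 participants per arm with paired scans (50/2 = 25 with an even split, less some who cannot be scanned), and an arm mean of 0 in SD units of change.
   - No judgement involved: shift 0.
   - One scan at −1.5 SD dropped in one arm: 1.5/19 = +0.08 SD.
   - Two such scans dropped in one arm: 3.0/18 = +0.17 SD.
   - 95% half-width of the between-arm difference before any exclusion: t(38) × √(2/20) = 2.024 × 0.316 = 0.64 SD.
   - The largest of these shifts is 0.17/0.64, about a quarter of the half-width.

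   The inputs are assumptions, and nothing in the article says that such exclusions will occur.

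**The case against.** The strongest reply is that the limitation is openly disclosed, that MRI is exploratory, and that pipeline and quality-control detail usually sits in a full protocol, analysis plan or local procedures that are not shown. Much of this stands. The article contains no contradiction here, and the absence of a described pipeline is not a fault. Disclosure does not answer the point, however. The article states as a design choice that MRI is unblinded, and the reasons it gives do not cover the stage at which masking is feasible.

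A second reply is that staffing is limited and that the Q-Motor analysis relies on an independent researcher. This also stands in part: the Q-Motor arrangement does not show that MRI could be masked with existing staff in the same way. Relabelling does not need a second person to read the scans, but it does need someone's time.

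A reader might infer more than the documents support:

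- **That operator bias is present, or that processors know the allocation.** The article does not say who processes the scans, how far the steps depend on an operator, or that processors see the allocation. Only a risk can be claimed.
- **That the bias could never be undone.** Face-to-face ratings cannot be repeated, but scans are stored and non-identifiable data are archived for 15 years, so relabelled scans could be reprocessed. Masking at the outset is simpler than repeating the work.
- **That masking is almost free.** No cost is given, and the plan cites limited resources. Low cost is plausible because data are already coded and an independent statistician exists, but this is a judgement.
- **That the check of cognitive and motor scores shares the problem.** These scores "will be quality-checked against the original record forms by other members of the research team". Nothing says the forms show the arm, and this is a check of data entry.

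**Conclusion.** The point holds as an avoidable risk, not as a demonstrated bias. The plan masks the analysis of one quantitative outcome and leaves another unmasked, for reasons that do not apply to offline processing. Its coding arrangement does not close the gap.

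The conclusion rests on two assumptions that the article neither confirms nor excludes: that at least one of segmentation, tractography and quality-control exclusion involves operator judgement, and that those doing it could know the arm. If either fails, little or no risk remains, and the article need only say so.

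The size is unknown. The hypothetical shifts of 0 to 0.17 SD are small against a half-width of 0.64 SD, but a shift of this kind is systematic and the confidence interval does not reflect it.

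The consequence is confined to the secondary, exploratory microstructure estimates and any later planning that uses them. A reader might take unblinded MRI to weaken the decision on whether a larger trial is feasible. It does not, because none of the rates behind that decision uses MRI data.

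**What to change.** Before any image processing:

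1. Relabel all scans with a second random ID, unrelated to the study and CUBRIC IDs and keeping each participant's two visits linked. The independent statistician who generates the allocation sequences should hold the key.
2. Complete segmentation, tractography, quality control (including any exclusions) and index extraction on the relabelled scans.
3. Lock the resulting data, and only then merge treatment arm.
4. Reword the Blinding (masking) section so that the stated limitation covers participants and face-to-face data collection, and says that MRI processing is masked.

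If this cannot be done, or if the pipeline is fully automated with fixed exclusion rules, say so and give that as the reason.

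The cost is a relabelling step, some of the statistician's time and a short delay before the unmasked comparison. No additional reader is needed. One limit remains: if the person who ran a scan also processes it, relabelling removes the identifier but not anything that person recognises.
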